### Analysis Plan

The cluster randomized trial design will be used by randomizing primary care physicians (PCP) into the intervention or usual care arms. Outcomes will be collected and analyzed at the patient level. We will examine assigned randomization against the computer-generated randomization scheme to ensure randomization validity. Patient characteristics between the two groups will be compared using mixed effects models for continuous variables and generalized estimating equations for categorical variables while adjusting for random PCP effects. We will examine the distributions of continuous variables and use alternative approaches such as transformation or nonparametric methods in cases of violation to the normal distribution assumption. We will also examine the frequency distribution of all categorical variables and adopt exact inference procedures in cases of zero or small cell size. Any baseline variable that is found to be significantly different between the two groups will be included as a covariate in the analyses outlined below.

An intension to treat approach will be used in the analysis of all outcome measures. Composite cognitive scores collected at 6, 12, 18 and 24 months will be used as the primary outcome variables in mixed effects models. An indicator variable for intervention group (intervention vs usual care), time, interaction between group and time, and baseline cognitive scores will be included as independent variables as well as significant factors from the baseline comparison. PCP will be used as random effects to adjust for within-physician correlations. Significant group and time interaction or significant group main effect will indicate differences in cognitive function between the two groups. If significant interactions between group and time are found, post-hoc analyses will be conducted to determine the times when the two groups have significantly different cognitive scores. A significant main group effect in the absence of a group-by-time interaction would indicate differences between groups in cognitive function at all follow-up time points.

In a second set of models, we will determine whether differences between groups were accounted for by decreases in total exposure to anticholinergics from baseline to 24 months. For each medication, standardized daily exposure will be calculated using standardized daily dose as in the study by Gray^7^ and validated in our prior work^14
17

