### Sample Size and Rationale

The sample size calculation was conducted using a mixed effects model and adjusting for the cluster randomization design. Assuming a within-subject correlation of 0.3, 0.2 and 0.1 for outcomes observed 6, 12 and 18 months apart, respectively, from the same individuals over time, 96 patients per group is required for 80% power to detect differences in composite cognitive scores of 0.6 SD at 24 months between the intervention and usual care groups with type I error rate at α=0.05 assuming linear trends in cognitive change in both groups. We further assume an intra-class coefficient (ICC) of 0.05 for primary care physicians and an average of 6 patients per physician. Accounting for the cluster design requires 120 patients per group to complete the trial. With an expected 30% attrition rate, we plan to enroll 172 patients per group into the study. Prior studies have reported mean differences in 1-year change of cognitive scores of 1.82 (SD 17) or 1.93 (SD 15) between those on definite anticholinergics versus those non-users. The effect sizes we used assume that our intervention will be able to detect a one-sixth reduction in expected cognitive decline if patients in the intervention group discontinue anticholinergics. Our assumption on the ICC is based on prior studies on prescribing patterns in physicians and practices.^58^

In Primary Aim 2, using the effective sample size of 96 patients per group accounting for the design effect from cluster randomization, we will have 85.6% power to estimate the confidence bands with half-width of 0.3 SD for the differences in symptom scores from PROMIS and HUI scores between the intervention and usual care groups during follow-up using the two-sample t-tests at the 0.05 level. Power estimates were calculated using the GLMPower and Power procedures in SAS software version 9.4 (SAS Institute, Cary, North Carolina).

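### Baseline score enters the primary model only as a main effect, so the group-by-time test gets almost no baseline adjustment; a baseline-by-time term would be a cheap, modest gain

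*Protocol article*

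**What the plan says.** The Analysis Plan section of the protocol article fixes the outcomes: "Composite cognitive scores collected at 6, 12, 18 and 24 months will be used as the primary outcome variables in mixed effects models". Baseline is therefore a covariate and not one of the modelled outcomes. The fixed effects are the group indicator, "time, interaction between group and time, and baseline cognitive scores will be included as independent variables", plus any factors that differ significantly between arms at baseline. For clustering, "PCP will be used as random effects to adjust for within-physician correlations". No product of baseline score and time is listed.

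The success rule has two routes: "Significant group and time interaction or significant group main effect will indicate differences in cognitive function between the two groups". A significant interaction also opens the post-hoc comparisons at single visits. The same section says that PROMIS and HUI scores will be modelled in a similar way.

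The Sample Size and Rationale section is the only place that says how scores relate over time: "Assuming a within-subject correlation of 0.3, 0.2 and 0.1 for outcomes observed 6, 12 and 18 months apart, respectively". It targets "differences in composite cognitive scores of 0.6 SD at 24 months between the intervention and usual care groups with type I error rate at α=0.05" and assumes that change is linear in both arms.

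**The concern.** Baseline is put into a longitudinal model to gain precision and to remove the effect of chance differences between the arms. With one slope for all visits it can do neither for the group-by-time test, because the same correction is applied to every visit and cancels when visits are compared. Other baseline variables added as main effects because the arms differ on them cancel in the same way.

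This matters because the interaction is one of two results that count as showing an effect, and a diverging linear trend is the pattern on which the trial was sized. If baseline predicts early visits better than late ones, a chance baseline difference fades during follow-up, and the fading enters the interaction estimate as though it were a treatment trend. The visit-level differences are also adjusted with one pooled slope, too shallow early and too steep late.

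**Working it through.** **Inputs.** From Sample Size and Rationale: correlations 0.3, 0.2 and 0.1 at 6, 12 and 18 months apart; "96 patients per group is required for 80% power"; 0.6 SD at 24 months; ICC 0.05; 6 patients per physician; 30% attrition. Assumed here: the same correlations apply from baseline to follow-up; the 24-month value, which is not stated, lies between 0 and 0.1; the SD is 1 at every visit; tests are two-sided.

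**The plan's own figures.** Design effect 1 + (6 − 1) × 0.05 = 1.25. 96 × 1.25 = 120. 120 / 0.70 = 171.4, rounded up to 172. These steps reproduce. The stated inputs do not pin down the 96: group-by-time calculations under different readings give 74 to 185 per arm, which straddles it. Nothing below depends on it being right.

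**Cancellation.** With baseline slope b and baseline difference d between arms, the adjusted difference at visit t is D(t) − b·d. Between visits s and t the change is D(t) − D(s), and b·d has gone. In 25 simulated trials per setting (20 physicians of 6 patients per arm, ICC 0.05):
- Complete data: adding the baseline main effect moved the group-by-time estimate by at most 1.4 × 10⁻¹⁵, which is rounding, with the same standard error. The group main effect moved by up to 0.08 SD.
- 30% dropout: the group-by-time estimate moved by at most 0.013 SD per visit step, against a standard error of about 0.06.

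**Precision.** Linear contrast c = (−3, −1, 1, 3) over the four visits.
- Variance: 20 + 2(0.3)(5) + 2(0.2)(−6) + 2(0.1)(−9) = 20 + 3.0 − 2.4 − 1.8 = 18.8.
- Covariance with baseline: −3(0.3) − 0.2 + 0.1 + 3r, where r is the 24-month correlation. This is −1.0 at r = 0 and −0.7 at r = 0.1.
- Share of variance removed by baseline-by-time: 1.0² / 18.8 = 5.3%, or 0.7² / 18.8 = 2.6%.
- Equivalent completers per arm: 120 / (1 − 0.053) = 126.7 and 120 / (1 − 0.026) = 123.2, so about 3 to 7 more.
- Power at 96 per arm: from 66.4% to 67.6–68.8% if the difference runs from 0.15 to 0.6 SD over the four visits; from 88.9% to 89.6–90.5% if it runs from 0 to 0.6 SD.
- With visit categorical (a 3-df test): 49.0% to 50.2–51.4%, and 76.1% to 77.4–78.6%.

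**Chance imbalance.** SD of the baseline difference: √(2 × 1.25 / 172) = 0.12 SD. A 1.96 SE imbalance, reached in 1 randomisation in 20, is 0.24 SD. The false change in the group difference from month 6 to month 24 is (0.3 − r)·d, that is 0.2d to 0.3d. At 0.24 SD this is 0.05 to 0.07 SD.

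**Conditional error of the linear test** (normal tail with shift k·√R² and SD √(1 − R²), where R² is the 2.6% to 5.3% above and k is the imbalance in SE):

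| Imbalance | Rejection rate under no effect |
|---|---|
| 0 | 4.4–4.7% |
| 0.5 SE | 4.5–4.8% |
| 1 SE | 5.0% |
| 1.5 SE | 5.4–5.7% |
| 1.96 SE | 5.8–6.7% |

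Averaged over randomisation it is 5%.

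**Pooled slope at 24 months.** The simple mean of the four slopes is (0.3 + 0.2 + 0.1 + 0) / 4 = 0.15, or 0.175 with r = 0.1. Set against 0 or 0.1 at month 24, the excess is 0.15 or 0.075. At a 0.24 SD imbalance this misplaces the 24-month difference by about 0.04 or 0.02 SD.

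**The case against.** A baseline main effect in a longitudinal mixed model is a standard and valid choice, and a journal article may leave the crossing of baseline with time to the full analysis plan. That lowers the weight of the point. It does not remove it, because the article lists the fixed effects and then defines success on them, and the listed model behaves as shown.

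The effect is small, and that stands. Even the 1-in-20 divergence of 0.05 to 0.07 SD is slight beside a design difference of 0.6 SD. The group main-effect route is baseline-adjusted as written.

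Three stronger readings are tempting, and the document does not support them.
- A reader might infer an inflated false-positive rate. The rates above 5% arise only at unusual imbalances. Below 1 SE, about two thirds of randomisations, the rate is at or under 5%, and overall it is 5%.
- A reader might infer that the plan contradicts itself. The stated lags of 6, 12 and 18 months are exactly those among the four follow-up visits. Extending them to baseline is plausible, but it is an inference.
- A reader might say that the adjustment cancels exactly in this trial. That needs complete data. With the expected 30% attrition the cancellation is near-complete.

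**Conclusion.** The point holds as a modest improvement to the primary model and not as an error that threatens validity. As listed, the model gives the group-by-time test essentially no baseline adjustment and gives visit-level differences one pooled slope. If baseline correlations decline as the sample-size section assumes for follow-up, and the 24-month value is 0 to 0.1, the loss is 2.6% to 5.3% of the variance of the linear contrast. A chance baseline difference also leaves a false trend of 0.2 to 0.3 times its size. If baseline predicts all visits equally, both are zero. The change is worth making because it costs almost nothing; its priority lies between optional and recommended.

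**What to change.** Add the interaction of baseline cognitive score with time to the primary model, with time coded as it is in the group-by-time term: linear if time is linear there, by visit if it is categorical. Do the same in the PROMIS and HUI models, each with its own baseline score. If the full analysis plan already has this term, no change is needed.

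The cost is one sentence of text and one extra fixed-effect parameter (linear time) or three (categorical visit). The baseline scores are already collected. The article expects data collection to end in July 2026, so the term can be fixed before analysis.

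The coding of time should not be changed on this account. At 96 per arm, under the plan's linear trend, the 3-df visit test has 49.0% power against 66.4% for the linear contrast, or 76.1% against 88.9%. That loss of about 13 to 17 points far exceeds the gain from better baseline adjustment.

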### Randomization procedures

In this cluster randomized trial, randomization occurs at the level of primary care provider in a 1:1 proportion between intervention and usual care using a randomization list with a computer-generated random scheme in random blocks of 4 or 6 stratified by healthcare system. Research staff are blinded to provider allocation status at the time of recruitment and throughout the study to avoid bias in data collection.

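### Read as an intercept, the PCP random effect gives the group-by-time test essentially no adjustment for physician clustering; a PCP-by-time term should be specified

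*Protocol article*

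**What the plan says.** Under Randomization procedures, "randomization occurs at the level of primary care provider in a 1:1 proportion between intervention and usual care". The Analysis Plan then describes the primary model. The outcomes are repeated: "Composite cognitive scores collected at 6, 12, 18 and 24 months will be used as the primary outcome variables in mixed effects models". The fixed part is listed thus: "An indicator variable for intervention group (intervention vs usual care), time, interaction between group and time, and baseline cognitive scores will be included as independent"; baseline factors found to differ are added. The random part is one sentence: "PCP will be used as random effects to adjust for within-physician correlations". The article names neither a PCP-by-time component nor a covariance structure for the repeated scores of one patient.

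The decision rule has two routes: "Significant group and time interaction or significant group main effect will indicate differences in cognitive function between the two groups". PROMIS and HUI scores are to be compared with similar models.

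Sample Size and Rationale gives "96 patients per group is required for 80% power to detect differences in composite cognitive scores of 0.6 SD at 24 months", under linear change in both groups. It then adds the clustering step: "We further assume an intra-class coefficient (ICC) of 0.05 for primary care physicians and an average of 6 patients per physician". That step raises the requirement to 120 completers per group.

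**The concern.** When physicians are randomised, every treatment contrast should be judged against variation between physicians in that same contrast. For the group main effect this is the PCP variance in average level, which a PCP intercept supplies. For group-by-time it is the PCP variance in change over time, which an intercept cannot supply.

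The article's own usage points to an intercept. The same kind of phrase, random PCP effects, is used for the baseline comparisons and for the total-exposure comparison. Neither of those models has a stated time term, so the phrase can only mean an intercept there.

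At stake is the type I error of one of the two routes to declaring a cognitive effect, and of the corresponding PROMIS and HUI tests. The sample size also includes a clustering penalty on a linear-trend calculation that the trend test, as described, would not carry.

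**Working it through.** **The plan's own clustering step.** Inputs from Sample Size and Rationale: ICC 0.05, 6 patients per PCP, 96 per group, 30% attrition.
- Design effect: 1 + (6 − 1) × 0.05 = 1.25.
- 96 × 1.25 = 120 completers; 120 / 0.70 = 171.4, so 172 enrolled per group, 344 in total.

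These figures reproduce exactly. The base figure of 96 was not recovered from the usual contrast formulas, but this point does not rest on it.

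**Does a PCP intercept reach the interaction?** Use 120 / 6 = 20 PCPs per arm, 6 patients each, visits at 6, 12, 18 and 24 months, unit variance and the plan's correlations ("Assuming a within-subject correlation of 0.3, 0.2 and 0.1 for outcomes observed 6, 12 and 18 months apart"). Take linear time with weights c = (−3, −1, 1, 3).
- The weights sum to zero, so a PCP effect that is equal at all visits contributes nothing to a patient's slope.
- Patient-level variance of the contrast: 20 + 2(0.3)(5) + 2(0.2)(−6) + 2(0.1)(−9) = 18.8. Slope variance: 18.8 / 20² = 0.047.
- Variance of the group difference in slopes: 2 × 0.047 / 120 = 0.000783, with no PCP variance in it.

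Generalised least squares at three PCP intercept variances (0.0526 = 0.05 / 0.95 corresponds to ICC 0.05):

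| PCP intercept variance | Group main effect | Group-by-time, complete data | Group-by-time, 30% dropout |
|---|---|---|---|
| 0 | 0.00702 | 0.000783 | 0.000955 |
| 0.0526 | 0.01228 | 0.000783 | 0.000958 |
| 0.2 | 0.02702 | 0.000783 | 0.000961 |

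The main-effect column rises by 2 × variance / 20, as it should (0.00702 + 2 × 0.0526 / 20 = 0.01228). The interaction is unchanged with complete data and moves by less than 1% with dropout.

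**Consequence if physicians differ in trajectory.** Let ρ be the slope ICC, the share of between-patient slope variance that lies between physicians. The article does not give it; the values below are assumed. The omitted design effect is D = 1 + (m − 1)ρ. The true level of a nominal two-sided 5% test is 2 × [1 − Φ(1.96 / √D)]; the article does not state sidedness, so two-sided is assumed.

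| ρ | D (m = 6) | Level (m = 6) | Simulated (m = 6) | Level (m = 4.2) |
|---|---|---|---|---|
| 0 | 1.00 | 5.0% | 4.9% | 5.0% |
| 0.01 | 1.05 | 5.6% | 5.4% | 5.4% |
| 0.02 | 1.10 | 6.2% | 6.3% | 5.7% |
| 0.05 | 1.25 | 8.0% | 8.0% | 6.9% |
| 0.10 | 1.50 | 11.0% | 10.6% | 8.8% |

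Here m = 4.2 is 6 enrolled per PCP less 30% attrition. The simulation used 20,000 runs. These levels assume that the within-patient covariance is modelled.

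**Check of the remedy.** Testing mean slopes at physician level gave a simulated level of 4.8% to 5.1%. Fitting the PCP-by-time term brought the ratio of true to model-based variance for group-by-time back to 1.0.

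**The case against.** The strongest reply is that silence is not exclusion. The article speaks of random effects and never says intercept only, and a journal article commonly leaves the detailed random-effects structure to an analysis plan. That stands as a limit: the point concerns the ordinary reading of the model as stated, not a proven omission from the full plan.

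A reader might infer that half of the primary decision ignores the physician randomisation. The article does not support that. The main effect is adjusted, and so is a between-group difference at a single visit, including 24 months, because the PCP intercept remains in it. Only the over-time contrast goes unadjusted.

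A reader might also infer that the false-positive rate certainly exceeds 5%. That is not supported either:
- With a PCP effect constant over time the test is valid. The only ICC given, 0.05, is based on prescribing patterns and is not stated for slopes.
- The article does not name a patient-level covariance either. If that is also absent, the two omissions partly cancel: simulated levels were 5.0% to 7.8% with linear time and 2.6% to 6.1% for the 3-df visit test, so the latter can be conservative.
- Differences between physicians in agreeing to, delaying or interrupting deprescribing do not show inflation. If deprescribing has no effect on cognition, uneven uptake creates no differences in cognitive trajectory.

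These objections make the concern conditional. They do not remove it, because setting PCP-by-time variance to zero in a physician-randomised trial is an assumption that the article neither states nor justifies.

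**Conclusion.** The point holds in conditional form. As ordinarily read, the stated PCP term gives the group-by-time test a clustering factor of about 1.00, while the sample size applies 1.25 to a linear-trend calculation. If patients of one physician share part of their trajectory, the interaction test is anti-conservative: with 6 patients per PCP, from about 5.5% at a slope ICC of 0.01 to about 8% at 0.05, and somewhat less with 4.2 per PCP. This rests on an intercept-only reading, a modelled within-patient covariance, two-sided testing and an assumed slope ICC. It is worth correcting because the randomised unit is the standard error term for this contrast and the change needs no new data.

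**What to change.** In the repeated-measures models for cognition, PROMIS and HUI, specify a random PCP intercept plus a random PCP-by-visit effect (or a PCP slope if time is linear), together with a within-patient covariance. Test group and group-by-time with PCP-based denominator degrees of freedom, for example Kenward-Roger. Pre-specify PCP-clustered standard errors with a small-sample correction as a sensitivity analysis, not as a fallback chosen after seeing a zero variance estimate. Do not extend the PCP-by-visit term to the comparison of total anticholinergic exposure: that outcome is cumulative and its model has no visit term, so a PCP intercept is the right structure there.

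The change takes a line or two in the model statement. The price is slightly wider intervals for the interaction and fewer degrees of freedom: about 38 with 40 PCPs (40 − 2), or about 55 if the 344 enrolled are spread at 6 per PCP (344 / 6 ≈ 57, less 2), against roughly 240 at patient level.

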Interim analyses will not be conducted to evaluate conditional power (futility) or efficacy, thus preserving the overall Type-I error probability regarding the efficacy of the intervention. Given the nature of an elderly study population, we expect study attrition in the form of participant death or withdrawal. Our proposed analysis plan using mixed effects models are robust under the missing at random (MAR) assumption that the probability for dropping out depends on participants’ characteristics and medical conditions. We will compare patients’ characteristics between the completers and non-completers to detect potential violation to the missing at random assumption. We will conduct sensitivity analyses to assess the potential impact of missing data using multiple imputation which allows the imputation of missing outcomes for those who drop out using data gathered from these patients at baseline and prior to drop-out. We will use SAS software version 9.4 (SAS Institute, Cary, North Carolina) or relevant updated versions for all analyses.

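### The primary rule accepts either of two tests, so if each is run at the plan's 0.05 the false-positive rate is about 7–10%, not the 5% said to be preserved

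*Protocol article*

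**What the plan says.** The Analysis Plan fits a mixed effects model to the composite at four visits: "Composite cognitive scores collected at 6, 12, 18 and 24 months will be used as the primary outcome variables in mixed effects models". The model has group, time, their interaction, the baseline score and a random physician effect. It then sets the criterion for a positive finding: "Significant group and time interaction or significant group main effect will indicate differences in cognitive function between the two groups".

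Two sentences say how each route is to be read. For the interaction: "If significant interactions between group and time are found, post-hoc analyses will be conducted to determine the times when the two groups have significantly different" scores. For the main effect: "A significant main group effect in the absence of a group-by-time interaction would indicate differences between groups in cognitive function at all follow-up time points".

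Later in the same section, the absence of interim analyses is described as "thus preserving the overall Type-I error probability regarding the efficacy of the intervention".

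Sample Size and Rationale gives the only significance level, "with type I error rate at α=0.05 assuming linear trends in cognitive change in both groups", and states 80% power "to detect differences in composite cognitive scores of 0.6 SD at 24 months". Sidedness is not stated; two-sided is assumed here.

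**The concern.** Two different tests can each deliver the primary claim. Reading the main effect only when the interaction is not significant gives no protection, because a significant interaction, or failing that a significant main effect, is the same event as at least one of the two being significant. Having no interim looks removes one source of inflation and leaves this one in place.

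The reading of the main-effect route is a separate fault. A non-significant interaction is not evidence that the effect is constant, so a significant average plus a non-significant interaction cannot support a difference at each visit.

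At stake is the error rate of the main efficacy claim in a trial meant to test a causal hypothesis. The Analysis Plan also carries similar models over to the PROMIS and HUI scores.

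**Working it through.** **Inputs.** From Sample Size and Rationale: α = 0.05; correlations 0.3, 0.2 and 0.1 at 6, 12 and 18 months apart; 96 per group before clustering; ICC 0.05; 6 patients per physician; 30% attrition. From the Analysis Plan: four visits and the either/or rule.

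**The plan's sample-size steps.** Design effect 1 + (6 − 1) × 0.05 = 1.25; 96 × 1.25 = 120; 120 / 0.70 = 171.4, so 172 per group. These steps reproduce. The base figure of 96 does not reproduce exactly with any test tried. The closest was a baseline-adjusted 3-df group-by-time interaction with differences of 0, 0.2, 0.4 and 0.6 SD over the four visits: 99 per group for 80% power, 78.6% at 96.

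**False-positive rate.** P(either) = 0.05 + 0.05 − P(both). It cannot exceed 10%. If the tests are independent it is 1 − 0.95² = 9.75%. Dependence lowers it, and how much depends on coding. Large-sample null results with the plan's correlations, from simulation (1,000,000 draws each):

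| Coding of time and main effect | Correlation of the two statistics | P(either) |
|---|---|---|
| Average over visits; 3-df interaction | – | 9.8% |
| Linear time, centred | 0 | 9.7% |
| Main effect at a reference visit (6 or 24 months); 3-df interaction | – | 8.9% |
| Linear time, main effect at 6 months | −0.71 | 8.3% |
| Linear time from month 0, main effect at month 0 | −0.86 | 7.4% |

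Each single test rejected in about 5.0% of null trials, so the excess comes from the rule. The linear rows also follow from the bivariate normal distribution. With correlation −0.858, P(both) = 2.6% and P(either) = 10 − 2.6 = 7.4%. Other correlation structures (compound symmetry 0.3 and 0.7, autoregressive 0.8, and 0.8/0.7/0.6) gave 7.8% to 9.8%. No coding gave 5%.

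**The every-visit reading.** Take 96 per group, the plan's correlations and, as an illustrative assumption, true differences of 0, 0.2, 0.4 and 0.6 SD.
- The average effect is significant in about 89% of trials and the 3-df interaction in about 77%.
- If the two were independent, the main effect alone would be significant in 0.89 × (1 − 0.77) = 20% of trials. Simulation gives 20.4%.

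In those trials the plan would report a difference at 6 months, where none exists. With assumed differences of 0, 0, 0.3 and 0.3 SD the figure is again about 20%.

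**A single 24-month test.** For 0.6 SD and 96 per group, z = 0.6 / √(2/96) = 4.157, and power = Φ(4.157 − 1.960) = Φ(2.197) = 98.6% (98.5% with the t distribution). Such a test needs only about 45 per group for 80% power.

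**Splitting alpha instead.** At 0.025 each, the rate is at most 5% (4.94% if independent). The base size rises by a factor of 1.211: 96 × 1.211 = 116.3, so 117; × 1.25 = 146.25, so 147; / 0.70 = 210 per group. Keeping 172 lowers power for the sized test from 80% to about 71%.

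**The case against.** The best defence is that the article gives no level for either test. The 0.05 appears only in the power statement, the Type I error sentence is about interim looks, and a separate SAP could name one test. It stands that 0.05 per test is inferred. But no other level appears in the article, and the either/or rule is stated outright rather than left open. As written, it contradicts an unqualified statement about the overall error rate.

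Several stronger readings are tempting, and the document does not support them.

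- **Visit tests as a third route.** A reader might infer that one post-hoc visit could make the trial positive. Visit comparisons follow only a significant interaction, so they describe a result already declared.
- **The interaction as always the weaker test.** With linear time and differences of 0 to 0.6 SD, the interaction and the average effect both have about 89% power at 96 per group. The interaction is weaker with categorical time (about 77%), or if the arms diverge from baseline to 0.15, 0.3, 0.45 and 0.6 SD (66% for the linear slope against 98% for the average).
- **The trial as sized on a 24-month test.** The 24-month figure is the effect quoted, but a simple contrast there needs about 45 per group, not 96. The stated size looks closer to an interaction test under a linear trend.
- **The every-visit sentence as resting on a non-significant interaction alone.** It also requires a significant main effect. The inference still fails, but it is a fault of interpretation and adds nothing to the Type I error figure.

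**Conclusion.** The concern holds. With each test at 0.05, the primary rule gives a false-positive rate of about 7–10%: 7.4% at the lowest coding found, and about 9.8% for the usual average-over-visits main effect. A reader might infer that the rate simply doubles to 10%. That is the upper limit, and the article does not fix the coding that would decide where in the range the trial falls.

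The figures assume two-sided tests, large-sample behaviour and the correlations tried. They cover only the either/or rule, not the choice of covariates by baseline significance or the visit comparisons.

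Separately, the claim that a main effect without a significant interaction "would indicate differences between groups in cognitive function at all follow-up time points" is not valid. Under the illustrative pattern above it would assert a non-existent 6-month effect in about one trial in five.

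**What to change.** Before unblinding, name one primary test at two-sided 0.05. A natural choice is the adjusted 24-month difference in the composite, from the mixed model with visit as a category and group-by-visit terms. It is the effect the sample-size section quotes, and power is about 98% at 96 effective patients per group in a simple two-sample comparison. A single prespecified interaction test, or one joint test of group and group-by-time, would also restore 5%; the power of the interaction depends strongly on the pattern of divergence. Splitting alpha is valid but costs sample size or power, as shown above.

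Make the remaining effects secondary. Replace the every-visit sentence with visit-specific differences and 95% confidence intervals. State which test the 80% power refers to.

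With a single test, the cost is wording and one fewer route to a positive result; no new data or participants are needed. The article expects data collection to run to July 2026.
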